#### Control condition

Participants will receive a series of five, weekly emails directing them to online modules containing general wellbeing information (HealthWatch website as described in the WellBeing Trial protocol [40]). Participants will complete questionnaires and interactive modules on information pertaining to health issues. The content of the modules will be as follows. Module 1: Diet and Nutrition. Module 2: Back pain. Module 3: Oral Health. Module 4: Calcium and Vitamin D. Module 5: Environmental Health. The modules also include items that ask participants about how these health issues impact on mental health.

### Sample size

Based on power calculations, an estimated minimum of 112 participants are required. Assuming a correlation of .5 between baseline and endpoint outcome measures, a 20% dropout, and an effect size of 0.43 [10], this sample size will have the power at 80% to detect differences at endpoint of .54 standard deviations (alpha = 0.05, non-directional test). Approximately 3000 babies are born per year at The Canberra Hospital. 20% of their mothers will score over 9 on the EPDS immediately after birth [33,41], yielding a potential pool of 600 women per year. Of these women, roughly 4% [42] will be clinically depressed and therefore excluded, leaving a potential pool of 576. Based on rates of recruitment from community samples, we anticipate that 25% of these potential participants will agree to participate in the study, yielding a sample of 144 women per year. Allowing for a further 10-20% unexpected drop-out after recruitment and before randomisation this should be sufficient to reach the target sample size of 112 participants.

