There has been substantial research into the prevention of PND. A recent review [8,9] found that prevention programs delivered postnatally only were more beneficial than those that included an antenatal component. Also, interventions delivered individually were more effective than those delivered to groups. Some prevention studies have focussed on models of care, where the delivery of service has been the focus, rather than the content of the intervention. Some of these models include postnatal layperson follow-up and home-based care. These strategies have not been particularly effective [8,9]. This is not surprising, given that the content of many of these interventions (support and/ or education about PND) was not necessarily selected on the basis of demonstrated efficacy in other contexts. Other studies that have used individual or group therapy based on Cognitive Behaviour Therapy (CBT) or Interpersonal Therapy (IPT), which are of known efficacy in *treating* postnatal depression, have been more successful in reducing symptoms and preventing the development of PND [10-14]. This type of intervention however, is expensive. Prevention involves delivering interventions to large numbers of women. To provide individual or group therapy to such numbers is costly and unlikely to constitute a feasible strategy for preventing PND.

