## Discussion

The aim of this trial is to assess the effectiveness of online CB Training for the primary prevention of postnatal depression in an at-risk sample. To our knowledge there are no published studies investigating the use of an online intervention to prevent PND.

We hypothesise that the MoodGYM prevention group will show a greater reduction in postnatal distress as measured by the EPDS. We also hypothesise that they will demonstrate lower levels of anxiety and stress and higher levels of parenting confidence than the control group.

The current study addresses many of the shortcomings of earlier trials. Many trials targeted “at-risk” women, but failed to screen out women with a current disorder. By contrast, the current study excludes women with a diagnosis of depression and thus is a true prevention trial not contaminated by treatment effects which inflate the effect size. Most previous PND prevention trials have used interventions that been previously untested either as *treatments* for PND or as treatments or preventive interventions for depression in general. Therefore the significance of a failure of the intervention to prevent PND is difficult to interpret. MoodGYM is an intervention of demonstrated efficacy both as a treatment, and as prevention for depression in a range of non-PND populations. Similarly, many of the studies using CBT incorporate additional interventions in the prevention program. Again, this complicates the interpretation of the study findings. We propose to use CB Training by itself rather than as part of a multi-component intervention. This will allow us to draw conclusions about the utility of Cognitive Behavioural strategies specifically for PND prevention.

The major limitation of the study is its small geographic coverage. For pragmatic reasons, the study will not, at this stage, be conducted in more than one site. The recruited sample may therefore not be representative of the broader population. Canberra’s population is better educated and of higher socio-economic status than the average for Australia. Further, since there have been no previous studies of online CB Training interventions for this population the recruitment rate is difficult to predict with certainty. A further potential limitation of the intervention is that it is not tailored to PND specifically. On the other hand, it possible that a generic intervention could have a normalising effect on symptoms.

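### The sample size assumes an effect of 0.43 but states 80% power only for 0.54 SD; with 112 randomised, power at 0.43 is about 52% to 64%

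*Protocol article*

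**What the plan says.** All of the calculation stands in the Sample size section of the protocol article. It opens by saying that "an estimated minimum of 112 participants are required". The next sentence lists the inputs: "Assuming a correlation of .5 between baseline and endpoint outcome measures", then "a 20% dropout, and an effect size of 0.43 [10" (the bracket is the literature citation). The same sentence concludes that "this sample size will have the power at 80% to detect differences at endpoint of .54 standard deviations", with "alpha = 0.05, non-directional test".

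The section then works through recruitment. It expects 144 women a year to agree, removes 10% to 20% for losses before randomisation, and finds this enough for a target of 112. The Abstract gives a different number, 175 participants to be recruited. The Analysis section plans a linear mixed model with group contrasts at post-intervention and at 3, 6 and 12 months.

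**The concern.** One sentence contains two effect sizes. The one with a literature source (0.43) is an assumption, and the one with a power statement (0.54 SD) has no source. A sample that just reaches 80% power for 0.54 SD has less than 80% for 0.43 SD, and the reader is not told how much less.

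This matters for reading a null result. If the intervention worked as well as the cited evidence suggests and only 112 women were randomised, the trial would miss the effect in roughly 36% to 48% of repetitions. A reader who takes the 80% at face value would give such a null result more weight than the design supports.

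**Working it through.** **Inputs from the Sample size section.** N = 112; two-sided alpha 0.05; power 80%; baseline-endpoint correlation r = 0.5; dropout 20%; assumed effect 0.43; detectable difference 0.54 SD.

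**Assumptions added here.** Allocation is 1:1, since the article gives no ratio. The 0.43 is a standardised difference in endpoint SDs, since the article gives it no unit. The 112 counts women randomised, because the section reaches it after removing losses before randomisation: 144 × 0.8 = 115 and 144 × 0.9 = 130, both just above 112.

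**SD factor s.** The article does not say how baseline enters the comparison, so both cases are shown.
- Endpoint only: s = 1. A change score at r = 0.5 gives the same, sqrt(2 × (1 − 0.5)) = 1.
- Baseline-adjusted: s = sqrt(1 − 0.5²) = 0.866.

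**Formulas (normal approximation).**
- n per arm = 2 s² (1.960 + 0.842)² / d²
- detectable difference = 2.802 × s × sqrt(4/N)
- power = Phi(d / (s × sqrt(4/N)) − 1.960)

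Final figures use the t-test, which differs by about one percentage point or less.

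**Step 1: reproduce the plan's figure.** For d = 0.54 and s = 1, n = 2 × 7.849 / 0.2916 = 53.8 per arm. The t-test gives 54.8, so 55 per arm and 110 in total, close to 112. For d = 0.43 / 0.8 = 0.5375, the t-test gives 55.3, so 56 per arm and exactly 112. Both use no dropout and no gain from the correlation.

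If dropout is instead applied to the number, d = 0.54 requires:
- adjusted: 2 × 41.4 / 0.8, about 103 randomised
- unadjusted: 2 × 54.8 / 0.8 = 137 randomised

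Neither is 112.

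**Step 2: what 112 randomised can detect.** Analysed: 112 × 0.8 = 89.6. Unadjusted: 2.802 × sqrt(4/89.6) = 0.592, or 0.599 by t-test. Adjusted: 0.592 × 0.866 = 0.513, or 0.518 by t-test. The stated 0.54 lies between them. Power at 0.54 is 71.5% unadjusted and 83.1% adjusted.

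**Step 3: power at 0.43.** Worked case, unadjusted, 89.6 analysed: 0.43 / 0.2113 = 2.035, and Phi(2.035 − 1.960) = 53.0%; the t-test gives 52.1%. By t-test throughout:

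| Randomised | Analysed | s = 1 | s = 0.866 |
|---|---|---|---|
| 112 | 89.6 (20% dropout) | 52.1% | 64.2% |
| 112 | 112 (no dropout) | 61.6% | 74.0% |
| 175 | 140 (20% dropout) | 71.4% | 83.1% |

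**Step 4: number needed for 80% power at 0.43 with 20% dropout.**
- Unadjusted: 86 per arm, 172 / 0.8 = 215 randomised.
- Adjusted: 65 per arm, 130 / 0.8 = 162.5, so 163 randomised.

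**The case against.** **The stated claim may be true.** The text never claims 80% power at 0.43; it claims it at 0.54. With 112 randomised, 20% dropout and baseline adjustment at r = 0.5, power at 0.54 is 83%, so the claim is met with a little to spare. It fails (71.5%) only if the correlation brings no gain. This stands. A reader might infer that the 80% statement is simply false, but the article does not support that. The defect is the unexplained move from one effect to another.

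**112 may not be the working number.** It is called a minimum, and the Abstract says 175. A reader might infer that the trial is underpowered whatever happens; that does not follow, since 175 randomised gives 71% to 83% at 0.43. The two numbers could even be linked: 175 × 0.8 × 0.8 = 112, if 175 counts recruits, 20% are lost before randomisation and 20% after. The article does not say so, and its recruitment text removes only the earlier loss before arriving at 112. On that reading 112 would be the number analysed, and power at 0.43 would still be 62% to 74%.

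**The mixed model could add power.** Averaging four follow-ups, with every correlation at 0.5 and a constant effect, would give about 91% for 0.43 with 89.6 analysed. But the section powers a difference at endpoint, and the Analysis section plans contrasts at each time point. No averaged contrast is stated.

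**The full protocol may explain the step to 0.54.** It may. The condensed statement still leaves readers with an 80% figure that does not apply to the assumed effect.

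**A further inference to avoid.** A reader might argue that 0.43 is too optimistic. The Background does place the cited source within the range of references given for individual or group therapy. But the weak controls criticised there are attributed to other references. The Discussion's remark that this "is a true prevention trial not contaminated by treatment effects which inflate the effect size" contrasts it with trials that did not screen out current disorder, and does not say the source of 0.43 was one of them. The documents do not settle the matter.

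**Conclusion.** The paragraph is wrong as written: it assumes one effect and reports power for another. With 112 randomised and 20% dropout, power at 0.43 is about 52% unadjusted and 64% baseline-adjusted. With no dropout it is 62% to 74%. It is therefore below 80% on every single-endpoint reading of 112.

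The 0.54 is not exactly reproduced from the stated inputs. That 0.43 / 0.8 rounds to 0.54 and leads to exactly 56 per arm suggests that dropout was used to enlarge the effect instead of the sample. This is an inference from the arithmetic, and the shortfall at 0.43 does not depend on it.

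The size rests on 1:1 allocation, on 0.43 being in endpoint SDs, and on 112, not 175, being randomised. At 175 the planning effect reaches 80% power after dropout only if the baseline-adjustment gain is realised.

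**What to change.** Use one target effect throughout, and say whether the 20% dropout was applied to the sample or to the effect. If 112 stays, the statement could read: *112 randomised (about 90 analysed) gives about 64% power for 0.43 SD and 80% power for 0.52 SD with a baseline-adjusted analysis (52% and 0.60 SD without).*

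Reconcile 112 with the Abstract's 175, stating for each whether it counts women recruited, randomised or analysed. If 175 randomised is the working target, give its power at 0.43 after dropout: 71% unadjusted, 83% adjusted. State the unit of 0.43 and whether the comparison is baseline-adjusted, because the power depends on both.

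The cost is a rewritten paragraph and a less favourable power statement. Conduct does not change if 175 randomised is already the target. If 112 is the target and 80% power at 0.43 is wanted, about 163 (adjusted) to 215 (unadjusted) women would have to be randomised.

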### Randomisation

Participants will be randomised to one of the two website conditions using a computer-generated algorithm that is replicable and validated. The start value for the seed will be determined from the current server time and will be recorded for replication. Randomisation will not be stratified and will occur automatically at the completion of the baseline survey by taking the next allocation of the generated schedule.

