## Methods/Design

### Design

A 2 (Condition) X 4 (Time) double blind, randomised controlled design is planned. Participants will be randomly allocated to either the online intervention or an online control condition. Outcomes will be assessed at baseline, post-intervention (6 weeks), 3 months, 6 months, and 12 months post-randomisation.

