5. *Risk factors* to be assessed by self-report include: health of infant, sex of infant, infant feeding status and satisfaction, infant feeding and sleep patterns, major life events, and difficulty of pregnancy and delivery. Each of these will be assessed with a single item. For example, “How satisfied are you with your birth experience with this baby” has a 5-point Likert Scale from ‘Very satisfied’ to ‘Very dissatisfied’. We will also assess level of maternal support using the Maternal Social Support Scale, and personal history of depression through the SCID. All risk factor items will be administered as part of an online battery, with the exception of the SCID.

6. Cognitive behaviour therapy literacy and stigma will be assessed using an online delivery of the CBT literacy scale and the Depression Stigma Scale (DSS) [38,39]. The CBT literacy scale has previously been successfully used to assess change in CBT knowledge following a MoodGYM intervention [20] and the DSS has adequate reliability and validity.

7. *Socioeconomic factors* will be assessed online, including self-reported age, marital status, education level, occupation, income, and parity.

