### Analysis

The outcome variables will be analysed on an intent-to-treat (ITT) basis using a linear mixed models analysis, a procedure which is able to handle missing data [43] with timepoints as a within groups factor and intervention condition as a between groups factor. A significance level of 0.05 will be used for all outcome variables. We plan to analyse contrasts between intervention and control groups at post intervention, 3-months, 6-months and 12-months follow-up.

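### Depression history and social support are measured before allocation, but neither the unstratified randomisation nor the stated model uses them; some precision may be lost (low severity)

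*Protocol article*

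**What the plan says.** All references are to the protocol article.

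- **Measures, item 5 (risk factors):** "We will also assess level of maternal support using the Maternal Social Support Scale, and personal history of depression through the SCID". On how they are collected: "All risk factor items will be administered as part of an online battery, with the exception of the SCID". Item 4 makes the baseline SCID a face-to-face interview.
- **Table 1 and Procedure:** support and personal history of depression are both scheduled at baseline. The SCID comes before the online baseline questionnaires, and randomisation follows them. Both values therefore exist before allocation.
- **Randomisation:** "Randomisation will not be stratified". Allocation follows automatically once the baseline survey is finished, "by taking the next allocation of the generated schedule". Neither the allocation ratio nor blocking is stated.
- **Analysis:** a linear mixed model on an intention-to-treat basis, "with timepoints as a within groups factor and intervention condition as a between groups factor". No risk-factor covariate is named and none is ruled out.
- **Design:** "Outcomes will be assessed at baseline, post-intervention (6 weeks), 3 months, 6 months, and 12 months post-randomisation". Baseline EPDS thus appears to enter the model as one of the time points.
- **Sample size:** a minimum of 112, with baseline-endpoint correlation 0.5, 20% dropout, effect size 0.43, and 80% power for 0.54 SD at two-sided alpha 0.05. The Abstract gives 175 participants.

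**The concern.** Past depression is not an exclusion; only a current depressive disorder is. The randomised women can therefore differ in a history that the plan itself treats as a risk factor, and likewise in social support. Neither factor is used at allocation or in the model as stated.

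Two things follow in a trial of about 56 women per arm. The arms may differ by chance on these factors, which would move the EPDS contrast in the one trial that is run. And any outcome variance that the factors explain beyond baseline EPDS stays in the error term and widens the intervals. Both can be reduced cheaply, because the data are in hand before allocation.

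**Working it through.** **1. The plan's own sample size.** Per arm, n = 2v(1.960 + 0.842)²/d², with v = 1 if baseline is not used and v = 1 - 0.5² = 0.75 if it is used as a covariate.

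- d = 0.54, v = 1: 53.8, so 54 per arm, 108 in all (110 by the t distribution). Dividing by 0.8 for dropout gives 135 (138).
- d = 0.54, v = 0.75: 40.4, so 41 per arm, 82 in all; with dropout 103.
- d = 0.43, v = 0.75: 63.7, so 64 per arm, 128 in all; with dropout 160.

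The stated 112 does not follow from all the stated inputs together. It is close only to the 0.54 SD case without dropout and without a gain from baseline. That is a separate matter. Below I take 112 as given, show 175 beside it, and use 112 × 0.8 ≈ 90 completers (45 per arm).

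**2. Chance imbalance.** Assumptions: simple 1:1 allocation, and a yes/no factor with prevalence p of 30-50% (the article gives no figure). SE of the arm difference = √(4p(1 - p)/N); normal approximation.

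| N | p | SE | P(at least 10 points) | P(at least 15 points) |
|---|---|---|---|---|
| 112 | 0.3 | 0.087 | 25% | 8% |
| 112 | 0.5 | 0.094 | 29% | 11% |
| 175 | 0.3 | 0.069 | 15% | 3% |
| 175 | 0.5 | 0.076 | 19% | 5% |

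If the factor is worth 0.5 SD (assumed), a 15-point difference moves the estimate by 0.15 × 0.5 = 0.075 SD, which is 0.075/0.54 = 14% of the detectable difference. For comparison, the standard error of the contrast with 45 per arm is √(2 × 0.75/45) = 0.183 SD.

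**3. Precision and power.** Take baseline EPDS as already used with r = 0.5 (v = 0.75) and 45 per arm. Covariates with partial R² multiply the residual variance by (1 - R²). R² is assumed.

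| R² | SE reduction | Power at 0.54 SD (normal) | Power at 0.54 SD (t) | Power at 0.43 SD (normal) |
|---|---|---|---|---|
| 0 | - | 84.1% | 83.3% | 65.4% |
| 0.02 | 1.0% | 84.8% | 84.0% | 66.2% |
| 0.05 | 2.5% | 85.9% | 85.1% | 67.6% |
| 0.10 | 5.1% | 87.7% | 86.9% | 69.9% |
| 0.15 | 7.8% | 89.4% | 88.7% | 72.4% |

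**4. Stratify, adjust, or both.** Simulation with 90 completers, 40% carrying the factor, and a factor effect of 0.5 SD. Power is at 0.54 SD.

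| Allocation | Analysis | Type I error | Power |
|---|---|---|---|
| Simple | Unadjusted | 5.1% | 82.9% |
| Simple | Adjusted | 5.2% | 85.3% |
| Stratified | Unadjusted | 3.5% | 83.2% |
| Stratified | Adjusted | 4.6% | 85.6% |

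The unadjusted estimate under simple allocation is unbiased. The gain comes from adjustment; stratifying on top adds 0.3 points. Stratifying without adjusting makes the test conservative.

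**The case against.** The strongest reply is that nothing here is an error. Unstratified randomisation is valid, and chance imbalance is already covered by the standard error and the 5% test. That stands. A reader might infer from the imbalance figures that the contrast is biased; step 4 shows that it is not.

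A second reply is that the article leaves room for covariates. A reader might infer that the model excludes them, but the Analysis section names two factors and forbids no others, and a covariate list is often left to the analysis plan. This also stands, so the point is an improvement to the method as stated and not a finding that adjustment is ruled out. The decision on stratification, by contrast, is fixed in the text.

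Three further readings go too far:

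- **That a marked imbalance is likely.** At 25-29% for 10 points with 112 women, and less with 175, it is possible but not the expected result.
- **That both factors sit in the computer system that allocates.** Social support does. Depression history comes from the SCID, which Measures excepts from the online battery. Table 1 has a separate row for it with no mode given, so this is not settled.
- **That power starts near 72%.** That is a two-sample t-test with no baseline information; it ignores the baseline EPDS measurement and the plan's own correlation of 0.5.

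Finally, the plan lists many risk factors and does not rank these two above the rest. That is fair; how much they predict beyond baseline EPDS is unknown.

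**Conclusion.** The point holds as a low-severity design improvement. Two named risk factors are known before allocation and are used neither there nor in the stated model, so some precision may be given up. Validity is not affected.

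The size is modest: a 1-8% smaller standard error, or power at 0.54 SD going from about 83-84% to 84-89%. This rests on an assumed partial R² of 0.02 to 0.15 beyond baseline EPDS, 90 completers, r = 0.5, and baseline EPDS being used as efficiently as a covariate would be. The imbalance figures rest on an assumed prevalence of 30-50%, and the shift of 0.075 SD on an assumed effect of 0.5 SD. The article gives none of these three quantities (partial R², prevalence, effect of the factor). At the Abstract's 175 participants, imbalance is less likely.

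**What to change.** **Main change, Analysis section.** Add one sentence that pre-specifies SCID history of depression (yes/no) and baseline MSSS score as fixed covariates in the mixed model for EPDS, DASS and KPCS, alongside baseline EPDS handled as a time point. Because baseline is one of the time points, the sentence should also say whether the covariate effects are held constant over time.

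**Optional, Randomisation section.** Stratify the computer schedule by SCID history, with random permuted blocks. This adds little beyond adjustment and should be done only together with it.

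**Cost.** The main change costs two extra model terms and no new data. The optional change needs a revision of the allocation program, and the face-to-face SCID result must be entered before the baseline survey closes. The order of steps in the Procedure section allows this, since the SCID precedes the survey.
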